#### Secondary endpoints

Comparisons between the 2 groups were performed for the secondary endpoints using Chi-square or Fisher’s exact tests for proportions and Student t or Mann-Whitney tests for continuous variables.

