### Sample size

On the basis of a unplanned hospital admission rate of 25% over a 3-month period [23] and taking into consideration the results of a study evaluating the impact at 8 weeks of medication review on admission to nursing home [24], we estimate a unplanned hospital admission rate of 10% in the experimental group. The initial sample size of 292 patients provided 90% power to detect this difference at a two tailed significance level of 0.05. Assuming possibly 25% of patients lost to follow-up, a total of 364 patients is required (182 per group) (Fig. 1).

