#### Secondary endpoints

Assessment of unplanned hospital admission at 6 months post-randomization will be complemented by the following endpoints:
Number of unplanned hospital admissions at 6 months post-randomization.Quality of life (QoL) of nursing home residents will be evaluated by the validated french version of EuroQol five-dimension three-level (EQ-5D-3 L) generic quality-of-life questionnaire [26, 27]. The questionnaire consists of two parts: the EQ-5D descriptive system and the EQ visual analogue scale (EQ VAS). The EQ-5D-3 L descriptive system comprises five dimensions as follows: mobility, self-care, usual activities, pain/discomfort and anxiety/depression. Each dimension has 3 levels: no problems, some problems, and extreme problems. The patient is asked to indicate his/her health state by ticking the box next to the most appropriate statement for each of the five dimensions. Each response generates a 1-digit number that represents the level selected for that dimension. The EQ VAS records self-rated patient health on a vertical visual analogue scale where the endpoints are labelled ‘best imaginable health state’ and ‘worst imaginable health state’. The EQ-5D-3 L questionnaire will be administered at the inclusion, at 3- and 6-month follow-up.Incidence of behavioral disturbances will be assessed by the validated french version of Neuropsychiatric Inventory (NPI) questionnaire at the inclusion, at 3- and 6-month follow-up [28]. NPI scoring is based on interviews with main caregivers. The NPI assesses the frequency (4-point scale) and severity (3-point scale) of 10 neuropsychiatric disturbances (delusions, hallucinations, agitation, dysphoria, anxiety, euphoria, apathy, disinhibition, irritability, and aberrant motor behavior), and a score from 0 to 12 is obtained for each scale by multiplying frequency by severity. The total NPI score is the sum of the subscale scores.The number of falls at 3- and 6-months post-randomization.The proportion of residents who will have been subjected to at least 1 potentially inappropriate prescription at the inclusion, 3 and 6 months. STOPP and START tool will be used for explicit criteria (French version 2). The implicit approach includes all available medical data, potential self-medication, and questions from the Medication Appropriateness Index [29].Nursing staff satisfaction with methods of medication administration to residents, number of oral medications dispensed, choice of galenic formulation, time spent on drug administration, and treatment dispensed to a patient consistent with that patient’s state of health. Satisfaction will be evaluated using 5-point Likert scales at the inclusion and at 3 months.Description of therapeutic recommendations which will have been proposed and GP’ adherence rate of its at 3- and 6-months.Characteristics of patients whose GP have taken account of TMR recommendations.Cost-effectiveness ratio of TMR versus standard care at 6-month follow-up (see details in Health Economic Analysis section below).The present study will also attempt to determine which organizational and psychosocial factors are likely to facilitate or on the contrary to hamper TMR development and acceptability (see details in Evaluation of Acceptability/Satisfaction section below).

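### Secondary endpoints are assigned unadjusted two-sample tests, which forgo the precision of the baseline EQ-5D and NPI values, and no count method is named for falls and admissions

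*Protocol article*

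**What the plan says.** Under Data management and analysis, the Secondary endpoints paragraph is one sentence. It assigns two families of tests: "using Chi-square or Fisher’s exact tests for proportions" and "Student t or Mann-Whitney tests for continuous variables". It names no covariate, repeated-measures model, count model or allowance for time observed.

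The list of secondary endpoints under Study aims shows what these tests must serve:

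- Quality of life: "The EQ-5D-3 L questionnaire will be administered at the inclusion, at 3- and 6-month follow-up".
- NPI: "questionnaire at the inclusion, at 3- and 6-month follow-up", with a total score defined as a sum of subscales.
- "The number of falls at 3- and 6-months post-randomization".
- "Number of unplanned hospital admissions at 6 months post-randomization".

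The Recruitment and randomization section gives every patient the same 6-month follow-up and stratifies randomization by Trivalle score. The Sample size section provides for attrition: "Assuming possibly 25% of patients lost to follow-up".

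More elaborate methods appear elsewhere. Logistic regression, a mixed model for centre and survival curves are listed under the primary endpoint. Repeated quality-of-life measures and reweighted estimators for censored data are listed under Health economic analysis.

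**The concern.** Two features of the secondary endpoints are left unused.

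First, a two-sample test on EQ-5D or NPI at a visit takes no account of where each resident started. In a scale measured on the same person months apart, baseline usually explains part of the follow-up variance, and removing that part costs nothing. The trial was sized for the primary endpoint only, so precision on the secondary endpoints is not guaranteed.

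Second, falls and admissions are counts that accumulate over time. A comparison of raw totals treats a resident observed for one month like one observed for six. If death or withdrawal were more frequent in one arm, that arm would show fewer events for that reason alone.

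**Working it through.** **Plan's own figure.** None is given for any secondary endpoint. The primary-endpoint size supplies a sample size to work with. For 25% vs 10%, two-sided 0.05 and 90% power:

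- n = [1.960·√(2·0.175·0.825) + 1.282·√(0.25·0.75 + 0.10·0.90)]² / 0.15² ≈ 132.8 per arm.
- With continuity correction: (n/4)·[1 + √(1 + 4/(n·0.15))]² ≈ 145.8, so 146 per arm, or 292 in all. This matches the article.

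**Baseline adjustment (EQ-5D, NPI).** The correlation ρ is an assumption. Per-patient variance in units of σ²:

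- Follow-up value: 1.
- Change score: 2(1 − ρ).
- ANCOVA: 1 − ρ².

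ANCOVA relative to follow-up values is therefore 1 − ρ². Relative to change scores it is (1 − ρ²)/[2(1 − ρ)] = (1 + ρ)/2.

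| ρ | Cut vs follow-up values | Equivalent extra patients | Cut vs change scores | Equivalent extra patients |
|---|---|---|---|---|
| 0.5 | 25% | 1/0.75: 33% | 25% | 1/0.75: 33% |
| 0.6 | 36% | 1/0.64: 56% | 20% | 1/0.80: 25% |
| 0.7 | 49% | 1/0.51: 96% | 15% | 1/0.85: 18% |

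Power for an assumed effect of 0.3 SD at 146 per arm is Φ(0.3·√(146/2)/s − 1.96), with s the square root of the variance above:

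- Follow-up values: 73%.
- Change scores: 73% / 82% / 91% at ρ = 0.5 / 0.6 / 0.7.
- ANCOVA: 84% / 89% / 95%.

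**Counts (falls, number of admissions).** Simulation with equal true rates in both arms. Assumptions: 182 per arm; gamma-Poisson counts with shape 1; mean 0.5 or 1.0 events per 6 months; time of loss uniform over 6 months; 4,000 trials per row (Monte Carlo standard error √(0.05·0.95/4000) ≈ 0.3 points). With a fraction f lost, mean exposure is 1 − f/2. The last column is a rate ratio using each patient's time at risk, with robust variance.

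| Loss by arm | Exposure ratio | Mean events | t | Mann-Whitney | Rate ratio |
|---|---|---|---|---|---|
| 25% vs 25% | 1.000 | 0.5 | 5.3% | 5.8% | 5.6% |
| 25% vs 25% | 1.000 | 1.0 | 4.9% | 4.9% | 5.3% |
| 20% vs 30% | 0.85/0.90 = 0.944 | 0.5 | 6.1% | 5.9% | 5.2% |
| 20% vs 30% | 0.944 | 1.0 | 6.6% | 6.5% | 6.1% |
| 15% vs 35% | 0.825/0.925 = 0.892 | 0.5 | 8.8% | 9.2% | 5.0% |
| 15% vs 35% | 0.892 | 1.0 | 11.1% | 12.5% | 5.3% |

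Further runs of the same model put Mann-Whitney at 4.4-5.4% (equal loss), up to 6.9% (20% vs 30%) and 9.3-12.6% (15% vs 35%). The error is therefore about 5%, 6-7% and 9-13% respectively. At 20% vs 30% the gap to the rate-ratio test is small and partly within simulation noise.

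The choice of method also affects power. With equal 25% loss, mean 1.0 and a true rate ratio of 0.7, power is 57% (t), 47% (Mann-Whitney) and 59% (rate ratio).

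**The case against.** The strongest reply is that two-sample tests on secondary endpoints of a randomized trial are a common and valid choice, and that an article may leave endpoint-level detail to an analysis plan not shown here. The first half stands: averaged over randomizations, these tests keep their 5% error. The second half does not remove the point, because the article does not leave the method open. It names the tests.

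Several further objections stand and limit the point:

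- The article does not say whether follow-up values or changes from baseline are tested. With change scores the gain from adjustment is smaller at the higher correlations, as shown above.
- It does not say that counts will be treated as continuous. That is inferred because no other family is named for a number. The abstract also calls 6-month admissions a rate, so they could be analysed as a proportion. Likewise NPI is introduced as an incidence, although a total score is defined.
- Some attrition is mitigated. The Discussion assigns data collection to research assistants to limit missing data, and the Health economic analysis section draws on hospital information departments for inpatient stays where needed. Admissions may thus be known after contact with the home is lost.

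The adjusted and time-to-event analyses under the primary endpoint, and the repeated quality-of-life measures under Health economic analysis, are not extended to the secondary comparisons and do not repair them.

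A reader might infer that follow-up is unequal by design, or that these tests generate false differences as a matter of course. The documents support neither. Follow-up is a fixed 6 months and becomes unequal only through death or loss. The 25% loss is not split by arm, and nothing stated says that it will differ.

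**Conclusion.** The point holds as a low-cost improvement to the secondary analyses, not as an error that invalidates them. For EQ-5D and NPI scores the stated tests forgo precision. The variance reduction available is 25% / 36% / 49% against follow-up values, or 25% / 20% / 15% against change scores, at assumed correlations of 0.5 / 0.6 / 0.7. Some gain against follow-up values exists for any non-zero correlation; its size rests on a figure the article does not give.

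For falls and number of admissions, no count method is named. If raw totals are compared, time at risk is ignored. That does no harm to type I error when loss is similar in both arms, and matters materially only if loss differs clearly: about 6-7% at 20% vs 30% and about 9-13% at 15% vs 35%. These splits, the event rates and the dispersion are all assumed.

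**What to change.** In the Secondary endpoints paragraph of Data management and analysis:

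- EQ-5D index, EQ VAS and NPI total score: ANCOVA, or a mixed model for repeated measures with visit and treatment-by-visit, including the baseline value and the Trivalle stratum used in randomization. Report the adjusted mean difference with 95% CI at 3 and 6 months.
- Falls and number of unplanned admissions: negative binomial regression with log(days at risk) as offset, reported as rate ratios with 95% CI. State whether 6-month admissions are analysed as a count, a proportion or both.

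The cost is a wording change made before the database is frozen and slightly more analysis. Baseline EQ-5D and NPI are already collected. The offset needs an end-of-observation date for each patient, and Table 1 already records visit dates. The offset corrects for length of observation but still assumes that the event rate is unrelated to the reason for leaving. The primary analysis and the sample size are unaffected.

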### Health economic analysis

Incremental cost-effectiveness ratios (ICER) will be used to compare the cost effectiveness of the experimental strategy with that of standard care. The ICER is the ratio of the difference in costs between groups to the difference in effectiveness. As recommended by the French National Authority for Health [30], incremental effectiveness will be measured in terms of quality-adjusted life years (QALYs), which is particularly relevant in this instance since TE associated with a reduction in unplanned hospital admission rates would have immediate impacts on patient QoL. These QALYs are determined by multiplying life years by a utility value associated with the health states experienced (corresponding to patient quality of life) during the period under consideration. Preference-based utility scores will be calculated using the EQ-5D-3 L questionnaire [26, 27].

The cost perspective taken in our economic analysis is that of the healthcare payer. The time horizon starts at the first baseline evaluation and ends at 6-month follow-up. This horizon is pertinent for recording immediate and relevant healthcare utilization and costs associated with the innovative strategy and represents a period during which all effectiveness and cost data will be accurately collected. The healthcare resources included will be those that are likely to differ between the experimental and control groups and will consist of: the TE intervention (including all categories of staff involved in data analysis and PPP writing, equipment required, time taken by coordinator/physician to collect and transfer data) and the healthcare costs generated by follow-up (including pharmaceutical medications and associated treatments, unplanned consultations and examinations, emergency department visits, inpatient stays differentiating between planned and unplanned hospital admissions, and transport costs). All resources will be collected from patient medical records and where necessary from referred hospital Departments of Medical Information (DIM) to identify exhaustive use of inpatient resources. Unit costs will be estimated using data from the French National Hospital Database and the national tariff. Medication costs will be obtained from the French Register of Pharmaceutical Specialties, an online database providing information on healthcare products. All resources will be valued in 2020/2021 euros, and the 6-month trial period means that no application of discount is required.

Descriptive statistics will be used to analyze effectiveness and cost variables, being both univariate and multivariate analysis (using non-parametric tests and bootstrap procedures respectively). Reweighted survival estimators and repeated measures of health-related QoL will be used in case of censored data. Probabilistic sensitivity analyses, using the non-parametric bootstrap method, will be carried out to generate mean expected ICERs and to determine whether uncertainty or variation in the data used affect the ICERs [31]. In addition, cost-effectiveness acceptability curves will be constructed to represent decision uncertainty surrounding cost-effectiveness estimates [32].

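### Univariate cost and QALY comparisons are assigned non-parametric tests, most naturally rank tests, which do not test the mean differences that the ICER uses (minor)

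*Protocol article*

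**What the plan says.** The Health economic analysis section defines the target: "The ICER is the ratio of the difference in costs between groups to the difference in effectiveness". Effectiveness is measured in QALYs. "The cost perspective taken in our economic analysis is that of the healthcare payer", and the horizon runs from baseline to 6 months. Uncertainty is handled by probabilistic sensitivity analyses which, "using the non-parametric bootstrap method, will be carried out to generate mean expected ICERs", together with acceptability curves.

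One sentence covers the separate analysis of the cost and effectiveness variables. It opens by calling the work descriptive and then assigns methods: "being both univariate and multivariate analysis (using non-parametric tests and bootstrap procedures respectively"). Its last word separates the two, so the univariate comparison is given the tests and the multivariate analysis the bootstrap. The test is not named there. Under Data management and analysis, Secondary endpoints, the article lists "Student t or Mann-Whitney tests for continuous variables", which makes Mann-Whitney the only non-parametric test it names for continuous data.

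The costed resources include "the TE intervention (including all categories of staff involved in data analysis and PPP writing, equipment required" and staff time for data transfer. They also include follow-up costs: medications, consultations, emergency visits, inpatient stays and transport.

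**The concern.** A payer's budget is mean cost times the number of residents, so the ICER numerator is a difference in arithmetic means. Mann-Whitney asks instead whether a randomly chosen experimental resident tends to cost more than a randomly chosen control. Under skewed costs these questions can have different answers, and this trial's cost structure pulls them apart. The intervention cost moves every experimental resident up a little. The saving from avoided admissions is large but falls on few residents, and ranks largely ignore its size.

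At stake is a report that prints a significant cost increase, or no detectable difference, beside an ICER numerator that shows equal cost or a saving. Cost-effectiveness at 6 months is a listed secondary endpoint, so readers will look at that p-value.

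**Working it through.** **Inputs from the article.** Admission risk is "a unplanned hospital admission rate of 25% over a 3-month period" in controls and 10% in the experimental group, with 182 randomised per arm. As a check on these inputs, the stated 292 was reproduced. The uncorrected two-proportion size is (1.960·√(2·0.175·0.825) + 1.282·√(0.25·0.75 + 0.10·0.90))² / 0.15² = 132.8 per arm. The continuity correction, (132.8/4)·(1 + √(1 + 4/(132.8·0.15)))², gives 145.8, so 146 per arm and 292 in total. The article states no figure for the economic tests.

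**Assumed inputs (none are in the article).** Mean admission cost is 4000 euros (lognormal, CV 0.8). Background 6-month cost has mean 1000, 2000 or 3000 euros (gamma, CV 0.5 to 1.0). The intervention costs F = 100 to 400 euros per experimental resident.

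**Why the two questions separate.** Take the limiting case of a background cost with no spread. Every experimental resident then costs more than a non-admitted control, and two admitted residents are close to a coin toss. So P(experimental > control) ≈ 0.75 + 0.25·0.10·0.5 = 0.7625, however small F is. The mean difference is F − 0.15·4000 = F − 600, a saving for any F below 600. Real background spread hides the uniform shift, so the size of the problem depends on F relative to that spread.

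**Equal true means.** The experimental admission risk is set to 0.25 − F/4000 (for example 20% at F = 200). The table gives the share of 2000 simulated trials in which two-sided 5% Mann-Whitney says the intervention costs more, at 182 per arm. Ranges show repeat runs.

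| Background mean, CV | F = 100 | F = 200 | F = 300 | F = 400 |
|---|---|---|---|---|
| 1000, 0.5 | 13–15% | 42–44% | 76% | 93% |
| 1000, 0.8 | 9–10% | 22–24% | 45–47% | 68–69% |
| 2000, 0.5 | 5% | 10% | 18% | 30% |
| 2000, 0.8 | 3% | 7% | 11% | 17% |
| 3000, 1.0 | 4% | 5% | 6% | 8% |

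A Welch test of means gives 2 to 3% in that direction throughout. With identical arms, total rejection was 5.7% for Mann-Whitney and 4.8% for Welch.

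**True saving.** The 25% and 10% are 3-month risks, but "The time horizon starts at the first baseline evaluation and ends at 6-month follow-up". Constant risk compounds to 1 − 0.75² = 44% and 1 − 0.90² = 19%, so both pairs are shown. The true saving is the risk difference times 4000, minus F.

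| Risks | Background, CV | F | True saving | Saving found: Mann-Whitney v Welch | Mann-Whitney says costlier |
|---|---|---|---|---|---|
| 25% v 10% | 1000, 0.5 | 200 | 400 | 1% v 45% | 7% |
| 25% v 10% | 1000, 0.8 | 200 | 400 | 3% v 45% | 2% |
| 25% v 10% | 1000, 0.5 | 400 | 200 | 0% v 15% | 83% |
| 25% v 10% | 2000, 0.8 | 200 | 400 | 11% v 32% | 0.4% |
| 44% v 19% | 1000, 0.8 | 200 | 790 | 60% v 82% | 0% |
| 44% v 19% | 2000, 0.8 | 200 | 790 | 64% v 72% | 0% |
| 44% v 19% | 1000, 0.5 | 400 | 590 | 4% v 61% | 2% |

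**Drug savings.** With 25% v 10%, background 1000 (CV 0.8) and F = 200, lowering experimental background cost by 10% or 20% raises Mann-Whitney detection of the saving to 13–14% or 39–40%. Welch finds it in 62–64% or 79–80%, and wrong-direction results are at most 0.4%.

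**The case against.** The strongest reply is that no conclusion hangs on this test. The ICER, its bootstrap and the acceptability curves are based on means, the sentence opens as description, and no decision rule refers to a univariate cost p-value. That stands, and it limits the point to the separate univariate comparisons. A reader might infer that the trial's cost-effectiveness result is itself biased against the intervention, but nothing in the article supports that.

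Second, rank test is an inference. The economic section does not name the test, Mann-Whitney comes from another section where it is paired with Student t, and a permutation test of a mean difference would also be non-parametric. This stands as a caution. But the sentence sets its tests apart from the bootstrap, and Mann-Whitney is the only candidate the article offers. If a mean-based test was intended, saying so removes the point.

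Third, the size comes from assumed costs. This largely stands. A reader might infer error rates far above 5% in all circumstances, or a routine reversal of sign. The tables do not show that. The excess is small with a background of 2000 to 3000 euros and a low intervention cost, and at compounded 6-month risks wrong-direction findings nearly vanish. Drug savings, which are plausible because the intervention adjusts prescriptions, reduce the effect further. In every setting with a true saving tabulated here, however, the rank test has less power than the test of means.

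**Conclusion.** The mismatch is real and minor. The article fixes a class of test for univariate cost and effectiveness comparisons that, read most naturally, does not address the mean differences in the ICER.

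Under equal mean costs and an intervention cost of 200 to 300 euros, false findings of higher cost run from about 7% (background 2000 euros, CV 0.8) to 44% or more (background 1000 euros, CV 0.5). A test of means gives about 2.5% in that direction. With a background of 3000 euros the excess is slight. Power to detect a true saving falls by about 10 to 60 points, depending on background cost, 6-month admission risk and intervention cost. All euro amounts are assumptions, so these figures show a range and do not predict this trial's result.

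The same mismatch holds in principle for QALYs but was not quantified.

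**What to change.** In the Health economic analysis section, replace the non-parametric tests for cost and QALY variables with the difference in arithmetic means between arms and a non-parametric bootstrap 95% CI, resampling residents within arm. Base any statement that the intervention changes cost or QALYs on that interval. Give medians and IQRs as description only, with no rank-test p-value.

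This changes one sentence. The bootstrap is already planned for the ICER, so no new data or software are needed. The small downside is wider intervals for skewed costs than a rank test might suggest.
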